| **Amount of Funding** | | | $76,080 (ARH) + $81,000 (philanthropy) | | | | |
| **Interests that the funding body has in the clinical trial** | | | The funders have a targeted interest in understanding what interventions help to reduce suicide risk in young people, however, none have any actual role in the trial conduct. | | | | |
| **Insurance for Clinical Trial** | | | | | | | |
| **Insurer** | | | **UNSW** | | | | |
| **Type of Insurance** | | | Clinical trial insurance was obtained via UNSW and a Certificate of Currency is provided (Appendix I). | | | | |
| **Confirmation of Insurance** | | | **Attached**  **In progress**  **To be submitted** | | | | |

# **Delegation of Clinical Trial Duties**

Responsibilities for the conduct and oversight for the trial are delegated to you as the Coordinating Principal Investigator. You may delegate trial related responsibilities to the listed Principal Investigator(s) and any trial-related personnel. All trial-related duties delegated by the Coordinating Principal Investigator or Principal Investigator(s) and trial-related personnel must only be delegated to those that are qualified by experience and training. Delegated responsibilities must be retained in the [UNSW Clinical Trial Delegation Log](https://research.unsw.edu.au/document/Clinical%20Trial%20Delegations%20Log.docx) (Appendix A). The UNSW Sponsor's Delegate is to be notified of the following:

- Protocol deviation reports outlined in the UNSW Research Misconduct Procedure.
- Any serious breach of Good Clinical Practice, the clinical trial protocol, the clinical trial standard operating procedures, or the human ethics approval that is likely to affect to a significant degree the safety or rights of participants or the reliability and robustness of the data generated in the clinical trial.
- Significant safety issues that are likely to (or have the potential to) affect to a significant degree the safety or rights of participants or the reliability and robustness of the data generated in the clinical trial.
- Urgent safety measures implemented to remove or prevent a significant safety issue.
- Safety reports relating to the continuation, suspension, or discontinuation of the clinical trial for safety reasons.
- Non-compliance with the protocol, SOPs, GCP, and applicable regulatory requirement(s) significantly affects or can potentially affect human subject protection or reliability of trial results significantly.
- Participant complaints or concerns received concerning the conduct of the research.
- Significant modifications to the clinical trial are likely to affect a significant degree the safety or rights of participants or the reliability and robustness of the data generated in the clinical trial.
- Addition of participating trial sites, contractual arrangements at participating sites or modifications to legal agreements.
- The intention to conduct the trial in other countries.

# **Trial Objectives and Purpose**

The LifeBuoy study has been designed to overcome challenges in: (i) the availability of effective digital health interventions for young people specifically for suicidal ideation AND (ii) how to promote engagement with such products to optimise therapeutic benefits. We plan to address these challenges by conducting a large 3-arm parallel randomised controlled trial (RCT) to test whether suicidal ideation can be reduced - and intervention engagement increased - using a therapeutic intervention delivered by smartphone application alongside a multicomponent digital engagement strategy.

Primary outcomes

Efficacy of the lifebuoy app: One primary objective of the current trial is to evaluate the efficacy of a mHealth application — LifeBuoy — for reducing suicidal ideation over time among young people relative to a control (non-therapeutic) app in a randomised controlled trial (RCT). This trial will answer questions that are important to making decisions about how (and whether) to scale up these interventions. More specifically, comparing 2-arms (both interventions combined vs. control arm), we will assess the efficacy of the LifeBuoy app in reducing suicide ideation among young people, as measured by the Suicidal Ideation Attributes Scale (SIDAS; [9]), relative to a placebo attention control condition. Changes in suicidal ideation will be assessed by comparing the intervention to the attention placebo control condition at 0-days (baseline, T0), 30-days (T1), 60-days (T2), and 120-days (T3).

Efficacy of the engagement strategy: the other primary objective is to explore whether participants who receive LifeBuoy + a digital engagement strategy report higher rates of app usage (measured in terms of the number of modules completed, number of app logins, and total time spent on the app) relative to the LifeBuoy-only condition. This trial will answer important questions about whether, and what, digital strategies improve user engagement, addressing key knowledge gaps in the digital health field. Previous research has shown that technology-based strategies can potentially improve user engagement [14]. However, a plausible reason why many such strategies fail is because they do not sufficiently address the needs of users and are thus not well-received [15]. Moreover, few studies have examined the efficacy of social media (e.g., Instagram) and blog posts in promoting greater engagement with DMHIs. More specifically, we will examine the efficacy of a digital engagement strategy – designed to optimise use of the LifeBuoy app – on app adherence (measured in the following ways: number of modules / activities / exercises completed; number and frequency of app log-ins; total time spent on the app) by comparing 2-arms: LifeBuoy + engagement strategy versus LifeBuoy-only at 0-days (baseline, T0), 30-days (T1), 60-days (T2), and 120-days (T3).

Secondary outcomes

1. To determine whether the LifeBuoy app reduces incidents of suicide attempt and non-suicidal self injury relative to the control condition at T1, T2, and T3.
2. To assess whether the LifeBuoy app reduces depression and anxiety symptoms relative to the control condition at T1, T2, and T3.
3. To examine whether the LifeBuoy app + engagement condition reduces suicidal ideation relative to the LifeBuoy-only condition at T1, T2, and T3.

# **Background Information**

Youth suicidal ideation and behaviour is a worrying public health issue due to its widespread prevalence and grave consequences. In Australia, suicide is the leading cause of death among individuals between 15 to 44 years of age [1]. In addition, suicidal ideation is relatively common among youth in the general population, with 12-month prevalence estimates as high as 24% in those aged 18 or younger [2]. Over one‐third of adolescents who experience suicidal ideation go on to attempt suicide [3]. Furthermore, it has been estimated that youth suicide carries significant economic costs, estimated to be $511M per annum [4]. High suicide rates among youth are exacerbated by their reluctance to seek help for psychological distress and suicidality. A recent review [5] reported that of 12,006 individuals with past-year suicide ideation, plans, and/or attempts, a weighted average of less than 30% sought help from mental health services. Lower rates of help-seeking were associated with being younger, being male, and cultural influences [5,6]. Potentially up to 70% of young people have not attempted or received access to mental health services. Traditional face-to face treatment services also have numerous economic, logistical, and personal barriers (i.e., stigma) that prevent most young Australians from accessing them [7].

Digital Mental Health interventions (DMHIs)—psychotherapeutic interventions delivered using digital (web- or smartphone-based) platforms—offer a new opportunity to improve access to support and provide high fidelity/cost-effective treatment, thereby addressing gaps observed in current population and health system approaches [8]. Importantly, recent meta-analytic evidence supports the effectiveness of DMHIs in mitigating suicidal ideation [9].

However, two significant issues warrant further investigation. At present, few digital interventions targeting suicidal ideation have been developed and rigorously tested, and none specifically for young people. This is despite estimates that 94% of young people own a smartphone and that they spend up to one-third of their day using electronic devices (phones, computers) [9]. Considering the levels of smartphone ownership and use, it is surprising that DMHIs remain relatively unexplored as a health solution in suicide prevention. Furthermore, the adoption of DMHIs in routine practice has been poor, in part, because of suboptimal rates of user engagement with these interventions [10-11]. Recent meta-analytic findings report that over 75% of users do not complete these interventions [12], and that attrition is especially salient among youth and young adult users [13]. Hence, there is a compelling need for the development and testing of effective strategies for enhancing user engagement with DMHIs.

To date, only one systematic review [14] has investigated the effectiveness of technology-based strategies in promoting user engagement with digital interventions (14 studies, n = 8,774). The review found that technology-based strategies—mostly in the form of prompts via email, text message or telephone—showed modest effects in promoting engagement than when no strategy was employed; however, the authors cautioned that the findings be considered in light of several limitations, including the small number of studies, small sample sizes in some of the studies, and heterogeneity in the methods employed across studies [14]. Importantly, only 8 of the 14 digital interventions discussed in the review were DMHIs. In summary, evidence of the effectiveness of engagement strategies in the context of DMHIs is scant and inconclusive.

#

# **Statement of Compliance**

The clinical trial will be conducted in compliance with the following guidelines and documentation:

- [ICH Guidelines for Good Clinical Practice (GCP)](https://www.tga.gov.au/publication/note-guidance-good-clinical-practice)
- [National Statement on Ethical Conduct in Human Research](https://nhmrc.gov.au/about-us/publications/national-statement-ethical-conduct-human-research-2007-updated-2018) (National Statement)
- As approved by the Human Research Ethics Committee (HREC), the clinical trial protocol is responsible for monitoring the trial's conduct.
- The responsibilities set out by the UNSW Sponsors Delegate.

The onsite or remote monitoring standard operating procedures as put in place by the clinical trial sponsor.

#

# **Trial Design**

This parallel design randomised controlled trial will involve three arms to answer the main objectives outlined in Section 4: 1) attentional control, 2) LifeBuoy only, and 3) LifeBuoy + engagement strategy. Participants will be followed up over four time-points: 0-days (baseline, T0), (0 days), 1-month (30- days (T1), 2-months (60- days (T2), and 4-months (120-days (T3).

The primary endpoint is change in suicidal ideation at T1 (day-30) relative to T0 (baseline, day-0).

The secondary endpoint is adherence to the LifeBuoy app across time, defined as the number of modules completed by participants at the T1, T2, and T3 post-baseline time-points. Participant module access and module completion data will be automatically collected via the LifeBuoy app.

The following flow chart (Figure 1) describes how an individual participant will progress through the phases of the research process:

[figure not shown]

*Figure 1: Study Process Flow*

Randomisation to treatment arms will occur on a 1:1:1 ratio using a block design using an automated web-based platform tailored for this project. All study assessments will be via electronic self-report. There are no outcome assessors.

Participants will have until the end of the 120-day period to access the apps. They will be prospectively followed up over four time-points: 0-days (baseline, T0), (0 days), 30- days (T1), 60- days (T2), and 120-days post baseline (T3). After completion of the T1 assessment, participants from the LifeBuoy (n=20) and LifeBuoy + engagement strategy (n=20) conditions will be invited to participate in a qualitative interview about the acceptability of the app and engagement strategy (n=40 in total). Participants will be recruited on a first-in first-served basis, and interviews will be conducted within 1-month of completing the T1 assessment to minimise memory failure relating to the engagement strategies.

The discontinuation criteria for individual participants will include if they experience a serious adverse event (Section 9.6 details withdrawal procedures).

The following accountability procedures for the intervention and control apps will apply:

- Software version control ensuring only approved/tested version of each intervention is used in the trial.

Randomization codes will be generated and retained automatically by the Black Dog Institute’s research engine.

Responsibility for holding and securing the randomisation list and performing any code break will be assigned in the Delegations Log. The list holder cannot be the Principal Investigator, or any other staff member involved in:

- day-to-day trial operations; or
- primary data analysis.

Because individual participants will be aware of, and able to disclose, the intervention to which they were allocated, codes may be broken only in the following situations:

- On completion of the primary data analysis, certified as complete by the Principal Investigator; or
- If required by the trial Data Safety Monitoring Board (see section 13, Ethics) in writing to the Principal Investigator.

Any code break shall be recorded in the Safety Monitoring Register and reported to the Sponsor).

Serious adverse events will be reported into the Data Monitoring Safety Board (DSMB, see Appendix). The trial manager will record the number of notifications at each assessment in the Report for DSMB document and will notify the DSMB every 3-months on how many alerts were triggered, and what follow-up was carried out. They will record these in a Case Report spreadsheet which will be securely stored on the UNSW server.

# **Sample Size**

The plan is to enrol 669 subjects to this trial. Sample size calculations were based on the primary aims. For Aim 1, to detect an expected minimum effect size of d=0.45 between the LifeBuoy intervention and the control condition on the primary measure of suicidal ideation (SIDAS), determined from the prior LifeBuoy trial (paper in review), with α = 0.01, power = 0.95, and assuming a 0.50 correlation between repeated measures, 112 subjects are needed in each condition. As a three-arm trial, with a 1:1:1 allocation, this means N=336 subjects are required to detect this effect. In addition, assuming an attrition rate of 25% in each group at our 30-day assessment based on the previous trial of LifeBuoy, 450 participants are needed (150 in each arm, rounded up). This sample size is sufficient to detect the expected effects associated with primary aim 1. For Aim 2, our recent systematic review of the engagement literature yielded three studies which were similar in design and population to our study34-36. The effect sizes in these studies varied from d = .04 to .53 reflecting a difference in user engagement when comparing a digital intervention only and the same digital intervention with an engagement strategy. Given the small number of studies, there is insufficient information to assume that effect sizes are normally distributed. Thus, the median effect size among the 3 studies (d = .38) was used as a benchmark. To detect an effect size of d=0.38 for primary aim 2 (alpha 0.01, power 0.95, assuming a 0.50 correlation between repeated measures, and 25% attrition), 223 participants are needed in each arm (rounded up). With a 1:1:1 allocation, this means N=669 subjects are required. Therefore, the larger sample size of 669 participants will be chosen to meet requirements of both primary aims. Qualitative interviews with 40 young people from the LifeBuoy and LifeBuoy + engagement group (minimum of 20 participants from the latter) will be recruited at the 30-day assessment time point, in which they will be asked whether they are interested to take part in an interview about their experience of the app and engagement strategy. This sample size will be large enough to reach saturation of qualitative themes.

# **Selection and Withdrawal of Subjects**

## Inclusion Criteria

Study inclusion criteria are as follows:

- 17 - 24 years old.
- Living in Australia.
- Fluent in English.
- Own and have access to a smartphone.
- Experienced suicidal thoughts in the past 30 days.

## Exclusion Criteria

Study exclusion criteria are as follows:

- Have been diagnosed with psychosis or a bipolar disorder in the past 30 days (because of increased risk to safety in this vulnerable group).

## **Recruitment Strategy**

The research team will identify a national community-based sample of participants for this project by running targeted social media advertisements in 2-weeks blocks until the full sample is recruited on Black Dog Institute’s Facebook page (see Appendix J for advertisement content).

The marketing/communications team at BDI will post targeted recruitment advertisement on Facebook to the following groups of users for the purposes of maximising visibility to relevant users: Male/Female 17-24, Australia, Interests > Additional interests, National Suicide Prevention Lifeline Suicide prevention, Beyondblue, Headspace, Lifeline (crisis support service), R U OK Day, SANE (charity). This strategy has been successfully used in many studies at the Black Dog Institute, including a survey study of anxiety during COVID-19, which recruited >5,000 in less than two months and an RCT of a mHealth intervention in young people, which recruited >450 in four days.

This initial contact to potential participants will not involve real or perceived coercion or pressure to participate because the researchers will not have direct contact with potential participants; recruitment, consent, screening, registration, and questionnaires are all scheduled and completed online.

In the absence of a response to completing the baseline questionnaire following registration, reminder/follow-up contact with potential participants will be undertaken by:

- Reminder invitations will be emailed to participants if they fail to complete the baseline questionnaire, or subsequent post and follow-up questionnaires.
- No more than 2 reminder invitations will be used to avoid potential coercion or pressure to participate.

Potential participants can indicate their interest in participating by clicking on the recruitment advertisement and following the directions online.

In the T1 assessment point, participants allocated to the LifeBuoy and LifeBuoy + engagement strategy conditions will be asked whether they are interested in participating in an interview to know more about their experience with the app and engagement strategies used during the study. Participants who have consented (Appendix D) will be contacted by email to arrange a time to attend an online interview (either telephone or videoconference). Questions of the qualitative interview have been listed in Appendix E.

## **Screening**

To determine whether a participant is eligible to take part in the study the research team will conduct a screening process, after they provide study consent. The eligibility survey will ask participants if they meet the inclusion/exclusion criteria. Participants who are deemed ineligible will be directed to a webpage thanking them for their time. This will include relevant support contact details. Participants who are eligible will be directed undertake the baseline assessment (Appendix).

## **Consent**

Participants will be provided with the PISCF (Appendix) online, once they click on the recruitment advertisement. Participants will be asked to read the PISCF and will have sufficient time to consider their participation because there is no time restriction before they consent and register to participate. Participants will be advised to contact the researcher(s) if they have any questions. The PISCF will be available for participants to download at the time of reading and from the study landing page if they wish. Once they are comfortable providing their consent to participate, participants will be asked to digitally sign the consent form and click ‘submit’, which will all be managed online via the trial portal (hosted on Black Dog Institute’s research engine). Upon receipt of their consent, they will be automatedly directed to register in the study.

This study will include participants aged 17 years to be able to consent themselves into this study as mature minors. To ensure that these young people are fully aware of the study’s intent, terms, and consequences, they will be asked to complete a 5-item Gillick Competency Task (Appendix D). The Gillick Competency Task comprises multiple choice responses to 5 questions relating to what the study is about, age for eligibility, what the study involves, how many surveys are included, and whether the respondent feels pressured to participate (please see questions and pass/fail responses below). If they fail this task (by answering any of the questions incorrectly), they will not be able to complete the survey and will be offered a message saying they are unable to successfully consent to this study and a list of help resources for mental health and suicide.

## **Withdrawal of Consent or Participant**

Participants may be withdrawn from the study if:

- They experience a serious adverse event that:
  - is attributable to a study intervention or procedure; or
  - means they can no longer participate in the study; or
- They withdraw consent to take part.
- We will not be replacing participants that are withdrawn from the study.

The team clinical psychologist will follow-up with subjects withdrawn due to experiencing a serious adverse event that was attributable to the study intervention or procedure. These participants will be contacted via email within 72 hours of withdrawing from the trial with a list of crisis contact numbers for support. In this email, participants will also be asked to respond to the email (by clicking ‘reply’) if they would like to receive a phone call from the team clinical psychologist during business hours (9:00 to 17:00 AEST). If they say yes, they will be contacted within the following 72 hours.

Participants can self-withdraw at any time by submitting to the study team the UNSW standard withdrawal form appended to the Participant Information Statement. No mechanisms for automated withdrawal (e.g. via the study app) will be provided. To ensure that data belonging to a participant who withdraws can be uniquely identified, their mobile number and email address will be solicited on the withdrawal of participation form. Excluding self-withdrawals, the decision to withdraw a participant will be made by the Principal Investigator.

Handling of participant data after withdrawal will depend on when a participant decided to withdraw from the study. Participants will have their data removed from the study if they withdraw or are withdrawn prior to completion of the baseline assessment. Reflecting the intention-to-treat principles informing the planned analyses of the trial, data from participants who withdraw after this point will not be discarded.

Those who complete baseline and are randomly allocated but then complete no subsequent surveys will not be treated as withdrawal but handled as missing data unless the specifically request to have their data withdrawn. Responsibility for confirming successful withdrawal of data will be assigned in the Delegations Log.

Non-identifiable data about withdrawals enabling aggregate reporting (e.g. counts by intervention assignment) will be retained in the Withdrawals Log which is part of the Safety Monitoring Register (see Appendix B). In addition, any participant withdrawal linked to an adverse event will be recorded to enable reporting of safety-related statistics. Participants who withdraw from the study will not be replaced and will not be followed up except per adverse event follow-up, if applicable (see Risk Management Protocol, Appendix G).

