In this trial a Serious Adverse Event (SAE) is o one or more of the following events and the event is not related to the trial intervention:

1. A participant reporting a suicide attempt or NSSI that requires medical care at any follow-up assessment time point.
2. If we become aware of a death of a participant during the trial, for any reason, this will also be considered a serious adverse event.

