# **Statistical analytical plan**

Mixed models repeated measures (MMRM) analyses, with maximum likelihood estimation and an appropriate covariance structure, will be used to evaluate longitudinal changes in suicidal ideation and secondary mental health outcomes between the LifeBuoy and attentional control arms. Where required, generalised linear mixed models with an appropriate link function will be used for the analysis of categorial variables. The primary outcome is severity of suicidal ideation, as measured by the Suicidal Ideation Attributes Scale [SIDAS], over time (baseline T0, 30-days T1, 60-days T2, and 120-days T3). The mixed model approach incorporates all available data, including participants with missing follow-up data points, under the missing-at-random assumption. Analyses will therefore accord with the intention-to-treat principle.

Descriptive statistics will be used to examine the level of engagement in three arms (LifeBuoy, LifeBuoy + engagement, and control). Engagement will be measured by the number of modules completed by participants. Participant module access and module completion will be automatically collected via the app.

Qualitative feedback on users’ perceived acceptability of the LifeBuoy app and engagement strategy will be examined through semi-structured interviews with a subset of participants (n=30 in total) and questionnaires in the survey. The interview data will be analysed using thematic analysis. An inductive approach, independent of a theoretical confirmative method will be used to identify and group themes. The researchers will then refine the themes and determine the final coding framework. Discrepancies will be resolved by a third researcher to ensure reliability of the process.

Any deviation from the original statistical plan will be described and justified in the final report.

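### Outcome surveys appear to stop for participants withdrawn after a suicide attempt or medically treated self-injury, which makes missing at random doubtful for their later outcomes

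*Protocol*

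**What the plan says.** **Follow-up after withdrawal.** Protocol, Withdrawal of Consent or Participant: participants who withdraw "will not be replaced and will not be followed up except per adverse event follow-up, if applicable". The follow-up described there and in the Risk Management Protocol consists of support emails and calls. No outcome survey is mentioned.

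**Who is withdrawn, and why.** The same section opens its list with "Participants may be withdrawn from the study if". One ground is a serious adverse event (SAE) that is attributable to the study or prevents further participation. Self-withdrawals aside, "the decision to withdraw a participant will be made by the Principal Investigator". Trial Design is broader: "The discontinuation criteria for individual participants will include if they experience a serious adverse event", with no attribution condition in that sentence, though it points to the withdrawal section.

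**What an SAE is.** Types of Safety and Monitoring lists "A participant reporting a suicide attempt or NSSI that requires medical care at any follow-up assessment time point", and also death. Its lead-in requires that "the event is not related to the trial intervention". Trial Objectives and Purpose makes suicide attempts and non-suicidal self-injury (NSSI) secondary outcomes at T1, T2 and T3.

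**Data and analysis.** On data already collected: "Reflecting the intention-to-treat principles informing the planned analyses of the trial, data from participants who withdraw after this point will not be discarded". The Statistical analytical plan uses a mixed model for repeated measures under missing at random, and concludes: "Analyses will therefore accord with the intention-to-treat principle".

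**The concern.** An outcome event can lead to withdrawal, and withdrawal ends outcome measurement. For someone withdrawn by the investigator, the gap comes from a study rule and not from the participant's refusal. Keeping the data already in hand is only part of intention-to-treat; the principle also needs outcomes to be sought from everyone randomised.

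At stake are SIDAS at later waves and repeat attempts or NSSI, which are secondary outcomes and rare enough that losing a few people matters. Safety information is affected too. Under Safety Analyses in the DSMB charter, attempts, NSSI and SIDAS above 20 come from the surveys, with participant emails as a further route for attempts and NSSI. The automated risk alert is also triggered by survey answers. Once surveys stop, later events in this group are seen only if volunteered.

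**Working it through.** **1. Does the no-follow-up sentence reach investigator withdrawals?** Its grammatical subject is participants who withdraw, and the section elsewhere distinguishes withdrawing from being withdrawn. Two features support the wider reading. Its exception for adverse event follow-up matches the contact promised to people withdrawn after an SAE, and its no-replacement clause repeats a rule already stated for people who are withdrawn. The wider reading is natural but not explicit.

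**2. What is lost, by when the event comes to light**
- Before day 30 (by email, a route named in the DSMB charter, or by self-withdrawal): T1, T2 and T3.
- In the T1 survey: T1 is kept, so the primary endpoint is intact; T2 and T3 are lost.
- In the T2 survey: T3 is lost.
- In the T3 survey: nothing is lost.
- Death: no survey could follow, so it is outside this point.

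**3. Is missing at random plausible here?** The mixed model conditions on observed SIDAS, including the high score at the triggering survey, which explains part of the missingness. As described in the protocol, it does not condition on the participant's answer about whether the study or app contributed (asked under Serious Adverse Reaction) or on the investigator's decision. If those carry information about later SIDAS beyond the observed scores, the assumption fails.

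**4. The plan's own figures, used for scale.** Sample Size gives d = 0.45 (Aim 1), d = 0.38 (Aim 2), alpha 0.01, power 0.95, correlation 0.50 and 25% attrition. I used a two-group repeated-measures F test with f = d/2, noncentrality f² × N × m / (1 + (m − 1) × 0.5) and N the total over two arms. The number of measures m is inferred, not stated.
- Aim 1, m = 4: 112 per arm (noncentrality 0.225² × 224 × 4 / 2.5 = 18.1); 112/0.75 = 149.3, rounded up to 150.
- Aim 2, m = 3: 167 per arm (noncentrality 0.19² × 334 × 3 / 2 = 18.1); 167/0.75 = 222.7, rounded up to 223; 3 × 223 = 669.

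The stated 112, 150, 223 and 669 reproduce. Nothing in this point rests on an error in them.

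**5. Size of the bias at a wave where these data are missing (illustration).** The documents give no SAE or withdrawal rate, so these inputs are assumptions: withdrawn share w₁ in the combined LifeBuoy arms (1-5%) and w₀ in control (1-2%), and unseen scores exceeding the model's prediction by s = 0.5 to 1.0 SD, equal in both arms.

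Bias towards the app = (w₁ − w₀) × s, in SD:
- 1% v 1%, any s: 0
- 2% v 1%, s = 1.0: 0.01 (2.2% of 0.45)
- 3% v 1%, s = 1.0: 0.02 (4.4%)
- 5% v 2%, s = 1.0: 0.03 (6.7%)
- 5% v 1%, s = 1.0: 0.04 (8.9%)
- 1% v 2%, s = 1.0: −0.01, that is, against the app

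With 446 LifeBuoy and 223 control participants, 5% v 1% means about 22 and 2 withdrawals.

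**6. Power.** For Aim 1 at T1, combined arms v control, 25% attrition leaves 334.5 v 167.25. Adjusting for baseline (SD factor √0.75), the standard error is √0.75 × √(1/334.5 + 1/167.25) = 0.082; 0.45/0.082 − 2.576 = 2.91, giving 99.8%. Five further points of loss in every arm give 99.7%. Without adjustment the figures are 98.5% and 97.8%. Power is not the issue.

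**The case against.** Much of the case on the other side stands, and it limits the point.

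- **A reader might infer that stopping the app means leaving the study.** It does not. Treatment of Subjects allows any amount of use, self-withdrawal needs a submitted form, and people who simply stop answering surveys are handled as missing data. Reminders for follow-up questionnaires are planned.
- **A reader might infer that the worst outcomes themselves vanish.** An SAE of this kind is normally reported in a follow-up survey that also carries SIDAS, and data obtained after baseline are kept. The loss concerns what happens afterwards.
- **A reader might infer a bias that always favours the app.** The documents do not support a direction. Control participants also have an app and surveys, the attribution question covers study participation as well as app use, and an SAE that prevents participation need not be tied to the app. If LifeBuoy reduces attempts, control could lose more high scorers.
- **Withdrawal after an SAE is discretionary and conditional**, so numbers may be very small.
- **The withdrawal form and consent pages are not at hand, and an SAP may exist.** The form might let people who withdraw themselves continue surveys. That would not settle investigator withdrawals, and an SAP can test sensitivity to missing data but cannot recover data never collected.
- **Further questionnaires may distress some of these people.** The protocol names questionnaire distress as a known risk. This is a fair limit on the remedy, and the fix carries an exception for it.

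**Conclusion.** The point holds in limited form. Read naturally, the protocol stops outcome collection for people withdrawn after an SAE who have not refused surveys, and the trigger is itself a trial outcome. Missing at random is therefore doubtful for these participants at T2 and T3 and for repeat events, and inferring intention-to-treat from the mixed model claims too much. The T1 primary endpoint is largely protected.

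The likely effect on the SIDAS contrast is small: about 0 to 0.04 SD in size under the assumed rates, zero when withdrawal and excess are equal across arms, and reversed in sign if control loses more. The rates and the 0.5-1.0 SD excess are assumptions, not figures from the documents. This is worth changing because the remedy is cheap and the data cannot be recovered later, not because the main result is in danger.

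**What to change.** - In Withdrawal of Consent or Participant, state that withdrawal from the intervention, including by the investigator, does not end outcome data collection. Continue the automated T1-T3 surveys unless the participant declines them or the surveys were themselves judged to have caused the harm. Include these data in the analysis.
- The withdrawals log already holds counts by arm. Split them into those who stopped the intervention and those who declined further surveys.
- In the Statistical analytical plan, do not present missing at random as the reason the analysis is intention-to-treat.
- Reconcile Trial Design, Withdrawal of Consent or Participant, and Types of Safety and Monitoring. They differ on whether any SAE or only certain SAEs are a ground for withdrawal, and an SAE is defined as unrelated to the intervention while one withdrawal ground rests on attribution to it. Which criterion should apply is for the investigators and sponsor to settle; this review proposes none.

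Cost: a short amendment and consent wording. The surveys are already automated and the sample size is unchanged. The real downside is that a few distressed participants would receive further questionnaires.
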